### Sample size

We estimate that at least 70% of children receiving current standard therapy for CSOM will (unfortunately) not be cured after 16 weeks of treatment. [8] The target enrolment was 280 participants. This study would have 90% power to detect an improved outcome in an additional 20% of children for each intervention (at the 5% significance level), assuming 10% loss to follow up or withdrawal.

### Data and specimen management and storage

All data collected was recorded on standardised forms in participant workbooks. Researchers enter data electronically into a MySQL database with secured Microsoft Access front-end as soon as possible after collection. All data are securely stored in a locked facility and microbiological specimens are stored securely at low temperature (−70C) in preparation for processing. Carriage data are entered directly onto the MySQL database by the laboratory scientists. Missing data and logic checks are carried out on all data with 10% of electronic data carefully cross-checked with paper forms.

### Statistical methods

All participants randomised are eligible for inclusion using principles of intention- to-treat (ITT) analyses of outcomes. Participants with complete data who completed all study visits are eligible for inclusion in the as-per-protocol analyses (APP). Baseline characteristics will be reported according to the treatment groups randomised: (i) povidone-iodine wash plus cotrimoxazole; ii) povidone-iodine wash plus placebo; iii) no povidone-iodine wash plus cotrimoxazole; and iv) no povidone-iodine and placebo. Based on CONSORT recommendations, there will be no inferential statistics for the baseline characteristics. Continuous variables will be presented by means, standard deviations, medians and interquartile ranges as appropriate. Counts and percentages will be used to describe categorical variables. Groups of size *N* = 140 will be compared, i.e. children who were randomised to povidone-iodine ear wash will be compared to children who were not, and children who were randomised to cotrimoxazole will be compared to children who were randomised to placebo. An interaction test to provide evidence of no interaction between the two interventions will be carried out first. Subgroup analysis will be assessed using interaction terms in a binomial regression models for binary outcomes and linear regression model for continuous outcomes at 4 and 12 months. The subgroups will include sex, age, category of CSOM and community.

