#### Primary clinical outcomes

The primary endpoint is the proportion of children with clinical failure of CSOM after 16 weeks (4 months) of treatment. A binomial regression with logarithmic and identity link will be used to estimate the main effects of the two interventions. Therefore, the relative risk and the risk difference, respectively, with their 95% confidence interval will be reported for the crude and adjusted estimates. The adjustment set will comprise of the stratification factors (age group and community) and the other intervention.

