#### Missing data

The number of participants with primary endpoint and other data available at required timepoints, will be reported. No data imputation for missing data will be carried out. Where reasonable, complete case analysis will apply. All analysis will be two-tailed and statistical significance will be set at *p* < 0.05, using Stata 15.1 (StataCorp, College Station, TX, USA).

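### The planned interaction test cannot provide evidence of no interaction: sized for main effects, the trial gives it about 37–43% power against a 20-point risk-difference interaction

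*Protocol article*

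**What the plan says.** The Statistical methods section compares each intervention across its margin, 140 against 140 children. On the factorial assumption it says: "An interaction test to provide evidence of no interaction between the two interventions will be carried out first". It names no scale for this test and no action after either result.

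Under Primary clinical outcomes, "A binomial regression with logarithmic and identity link will be used to estimate the main effects of the two interventions". Both relative risks and risk differences are therefore reported. The adjusted estimates include the stratification factors and the other intervention, and no interaction term is listed.

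The Sample size section assumes that "at least 70% of children receiving current standard therapy for CSOM will (unfortunately) not be cured after 16 weeks of treatment" and states: "This study would have 90% power to detect an improved outcome in an additional 20% of children for each intervention". It gives no power for an interaction. The Missing data section specifies complete-case analysis without imputation and two-tailed testing at 5%.

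**The concern.** The sentence gives the test a purpose that it cannot serve. Failing to reject the hypothesis of no interaction does not support that hypothesis unless the test had a good chance of rejecting it, or the confidence interval excludes interactions that matter. A 2 × 2 trial sized for its margins usually offers neither.

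The interaction bears on the trial's own question. The Abstract and Background both say it is unclear whether combining treatments brings any benefit. If the two adjuncts substitute for each other, the pooled effect of each understates what it does alone and overstates what it adds to the other. A report that read a non-significant test as absence of interaction would hide that difference.

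A secondary point concerns scale. Main effects are planned on both the ratio and the difference scale, and the test is not tied to either. If both adjuncts work, no interaction on one scale means some interaction on the other.

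**Working it through.** **Inputs from the article.** Enrolment is 280, loss 10%, failure on standard therapy 70%, target improvement 20 points, and alpha two-sided 5%. Evaluable: 280 × 0.9 = 252, or 126 per margin.

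**Assumptions, because the article does not give these figures.** Allocation is equal over the four arms, so each cell has 252/4 = 63. Cell failure rates are written in the order neither / wash only / cotrimoxazole only / both.

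**The article's own figure.** For 70% against 50% with 90% power, n per margin = (1.96·√(2·0.6·0.4) + 1.2816·√(0.21 + 0.25))² / 0.20² = 124. The total is 248, and 248/0.9 gives 276 enrolled, close to 280. At 126 per margin the power is 90.5%, so the stated 90% reproduces. If both adjuncts work additively, the margins are 60% against 40% and power is 89.3%.

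**Power of the interaction test, 70/50/50/50%.**
- Risk-difference scale: estimate = 0.70 − 0.50 − 0.50 + 0.50 = 0.20. SE = √[(0.21 + 0.25 + 0.25 + 0.25)/63] = √(0.96/63) = 0.123. Power ≈ P(Z > 1.96 − 0.20/0.1234) = 36.7%. A simulation of 200,000 trials gave 36.8%.
- Log relative-risk scale: estimate = ln[(0.70 × 0.50)/(0.50 × 0.50)] = ln 1.4 = 0.336. SE = √[(0.3/0.7 + 1 + 1 + 1)/63] = 0.233. Power is 30.3% (simulation 30.2%).

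**Other layouts with a 20-point risk-difference interaction, 63 per cell.**

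| Cells (%) | Power, risk difference | Power, log RR |
|---|---|---|
| 70/50/50/50 | 37% | 30% |
| 70/60/60/70 | 39% | 38% |
| 70/70/70/50 | 40% | 42% |
| 70/50/70/70 | 40% | 42% |
| 70/50/50/10 | 43% | 85% |

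The last row is extreme, and its 85% applies only on the log scale. With no loss at all (70 per cell), the first layout gives 40% on the risk-difference scale.

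**Precision.** With SE 0.123, the 95% confidence interval half-width is 1.96 × 0.1234 = 24 points. With the same SE, 80% power needs an interaction of (1.96 + 0.84) × 0.1234, about 35 points. For 80% power at 20 points, n per cell = 0.96 × (1.96 + 0.8416)²/0.20² = 188.4, rounded up to 189. That is 756 evaluable, or 756/0.9 = 840 enrolled.

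**What a missed interaction conceals.** In 70/50/50/50% each adjunct alone lowers failure by 20 points and adds nothing to the other. The margin without a given adjunct is (70 + 50)/2 = 60% and the margin with it is (50 + 50)/2 = 50%. The pooled effect is therefore 10 points, with 36% power at 126 per margin.

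**Scale.** With 70/50/50% in the first three cells, no additive interaction needs 50 + 50 − 70 = 30% in the combination cell. No multiplicative interaction needs 0.50 × 0.50/0.70 = 35.7%. Both nulls hold together only if (p00 − p10)(p00 − p01) = 0, that is, if at least one adjunct has no effect when given alone. In practice the mismatch is modest. By simulation, an exactly additive truth is rejected about 9% of the time on the log scale, and an exactly multiplicative truth about 8% on the difference scale, against a nominal 5%.

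**The case against.** A reader might infer that a non-significant test formally licenses the pooled analysis and that a significant one would block it. The article does not say so. The marginal comparisons and the primary model are both stated without condition, and the sample size rests on them. By randomisation, each marginal contrast validly estimates an effect averaged over the other factor even when there is an interaction. This part of the objection stands: the position of the test and its stated purpose invite a gate, but no gate is written.

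A reader might also infer that the null hypothesis cannot be true on both planned scales. That is too strong. It fails whenever one adjunct is inert when given alone, which a trial of uncertain treatments cannot exclude. The article also names the two links for estimating main effects, not for the interaction test.

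It is fair, too, that low interaction power is common to factorial trials sized on their margins, that the article's own power figure is correct, and that 37% comes from an assumed layout. A condensed article may leave the scale of the test and the four-cell table to a fuller document. None of this rescues the purpose clause. It states an inference that the test cannot support, and across the layouts tried, power on the risk-difference scale stays below one half.

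**Conclusion.** The statement is wrong as written. A non-significant interaction test in this trial would not be evidence of no interaction. Power against a 20-point risk-difference interaction is about 37% for 70/50/50/50% and 37–43% over the layouts examined. On the log relative-risk scale it is 30–42% for most of them. The half-width of about 24 points means that a null finding would commonly leave interactions as large as the target effect inside the interval.

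These figures rest on 63 evaluable children per cell, equal allocation, unadjusted Wald tests and assumed cell rates. The consequence is for interpretation: pooled effects of 10 points could be reported as free of interaction when each adjunct alone gives 20. The marginal comparisons themselves are not invalid, and the stated 90% power is not in error. The scale point is real if both adjuncts work, but secondary.

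**What to change.** - Delete the clause that gives evidence of no interaction as the purpose of the test.
- State that the marginal main effects are primary whatever the interaction p-value.
- Report the interaction as an estimate with its 95% confidence interval on one named scale. The risk difference matches the sample-size target.
- Show the failure proportion in each of the four cells, and the effect of each adjunct with and without the other.
- State that a non-significant interaction will not be interpreted as absence of interaction.

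The cost is a few sentences and one table, with no new data and no change to the sample size or primary model. The Trial status section reports that data cleaning has begun and some data collection continues, so the wording can be settled before analysis.

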#### Primary clinical outcomes

The primary endpoint is the proportion of children with clinical failure of CSOM after 16 weeks (4 months) of treatment. A binomial regression with logarithmic and identity link will be used to estimate the main effects of the two interventions. Therefore, the relative risk and the risk difference, respectively, with their 95% confidence interval will be reported for the crude and adjusted estimates. The adjustment set will comprise of the stratification factors (age group and community) and the other intervention.

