### Randomisation

Eligible children whose parent or guardian provided signed informed consent were randomised to one of the four treatment options according to a computer-generated sequence. This was obtained by a phone call (interactive voice response system) to the NHMRC Clinical Trial Centre (CTC). Children were stratified according to community and age (<4y, 4-10y, >10y) using a minimisation procedure**.** The allocation sequence was concealed from all investigators throughout the study. Study staff were blinded to the oral component of the treatment at randomisation and follow-up assessments. However, it was not possible to blind the topical treatment groups. All laboratory staff are blinded. The randomisation of an individual participant would only be unblinded in emergency situations where the chief investigator and study’s medical monitor feels the emergency cannot be adequately addressed without knowing which treatment was delivered.

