### Outcome measures

The primary outcome measure was the proportion of children with clinical failure after 16 weeks (4 months) of treatment. Clinical failure was determined by clinical examination for the presence of any ear discharge. Additional secondary outcome measures at 4 months and 12 months included: i) hearing level, determined by audiometry (performed by trained audiologists) and summarised as the pure tone 4 frequency average hearing level at 500, 1000, 2000 and 4000 Hz in the better and worse hearing ears; ii) failure to improve (determined by perforation size and amount of discharge); iii) change in perforation size and amount of discharge (determined by comparison of standardised assessment at baseline with end of study); iv) time to cessation of discharge (determined by review of health records); v) adherence to recommended management including attendance for specialist review (determined by review of health records); vi) presence of recognised bacterial pathogens in nose and ear discharge (determined by standard microbiological culture and antimicrobial sensitivity methods); vii) complications (defined as development of a related illness requiring additional medical treatment); and viii) side effects (defined as development of illness requiring cessation of prescribed treatments). Additional secondary outcomes at 4 months and 12 months from randomisation included the proportion of children with any carriage of pneumococci and any carriage of vaccine or non- vaccine serotype pneumococci and any carriage of NTHi. All children were followed up for any adverse events (AE) and serious adverse events (SAE) by reviewing the child’s clinic and hospital records and asking the parents about any side effects of the treatments between and at visits. We documented any contact the family or child had during the study with the clinic or hospital, including all relevant investigations and treatments. Regular, scheduled home visits, phone calls, SMS texts and social media contact with the families were made and recorded by study nurses or community researchers to support and promote participant retention; and monitor adherence.

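### The primary adjusted model is valid and adequately powered, but it omits baseline severity measures the trial already collects and so gives up a modest amount of precision

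*Protocol article*

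**What the plan says.** Under Primary clinical outcomes, the article specifies the model: "A binomial regression with logarithmic and identity link will be used to estimate the main effects of the two interventions". Relative risk and risk difference are given "with their 95% confidence interval will be reported for the crude and adjusted estimates". The covariates are a closed list: "The adjustment set will comprise of the stratification factors (age group and community) and the other intervention". These match the allocation scheme under Randomisation: "Children were stratified according to community and age (<4y, 4-10y, >10y) using a minimisation procedure".

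Severity enters elsewhere. Under Outcome measures, change in the perforation and in the discharge is a secondary outcome, "determined by comparison of standardised assessment at baseline with end of study", so both are measured at entry. Under Statistical methods, a severity-type variable is listed for interaction tests only: "The subgroups will include sex, age, category of CSOM and community". The primary endpoint is defined for the child: "Clinical failure was determined by clinical examination for the presence of any ear discharge".

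Under Audiology outcomes, by contrast, hearing level is adjusted for its own baseline value by ANCOVA.

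**The concern.** Three features of the article suggest that severity belongs in the primary model.

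- **The article treats severity as relevant to treatment success.** The Background reports a regimen that worked in about 75% of children in one earlier trial, against 70% failure in the group's own previous trial. It then cautions that disease severity differed between those children and the ones now living in remote NT communities.
- **Severity was not a minimisation factor.** Balance on it is left to chance.
- **Baseline adjustment is accepted for hearing.** Every child enters with CSOM, so the binary primary endpoint has little or no baseline value of its own. Perforation size and discharge amount are the nearest equivalent.

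What is at stake is the width of the intervals for the two main effects, and how far the realised estimates reflect a chance difference in severity. Recruitment is closed (Trial status), so the model is one of the few remaining places to gain precision.

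**Working it through.** **Inputs from the article.** Failure 70% v 50%, two-sided alpha 0.05, power 90%, 280 children, 10% loss (Sample size; Missing data for sidedness). Comparison groups of 140 (Statistical methods), hence 140 × 0.9 = 126 evaluable per group.

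**Input not in the article.** R2, the share of outcome variance within treatment groups that the added covariates explain. It is assumed, over 0.02 to 0.20.

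**1. Reproduce the stated design (no covariates).**

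n per group = [1.960 × √(2 × 0.6 × 0.4) + 1.282 × √(0.21 + 0.25)]² / 0.20² = 124. The total is 248, and 248 / 0.9 = 276 after rounding up, against 280 stated.

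Power at 126 per group = Φ{[0.20 − 1.960 × √(0.48/126)] / √(0.46/126)} = Φ{(0.2000 − 0.1210) / 0.0604} = Φ(1.308) = 90.5%. With a continuity correction it is about 88%.

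The stated 90% therefore holds without help from covariates.

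**2. Gain from adding severity.** The standard error is multiplied by √(1 − R2), which is equivalent to 126 / (1 − R2) children per group. The starting half-width is 1.96 × 0.0604 = 11.8 points.

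| Assumed R2 | 95% CI half-width (points) | Power |
|---|---|---|
| 0 | 11.8 | 90.5% |
| 0.02 | 11.7 | 91.0% |
| 0.05 | 11.5 | 91.8% |
| 0.10 | 11.2 | 93.1% |
| 0.20 | 10.6 | 95.5% |

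**3. What those R2 values mean.** For one binary covariate with prevalence q and a risk gap g, R2 ≈ q(1 − q)g² / 0.23, where 0.23 is the mean of 0.21 and 0.25.

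- q = 0.4, g = 0.25: 0.24 × 0.0625 / 0.23 = 0.065, power 92.2%.
- q = 0.5, R2 = 0.20 needs g = √(0.20 × 0.23 / 0.25) = 0.43. The top of the range therefore requires strongly prognostic covariates.

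**4. Check by simulation.** 252 children, two binary covariates with prevalence 40% and 50%, 4,000 replicates, least-squares risk difference with robust standard errors.

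| Risk gaps (points) | Power without covariates | Power with covariates |
|---|---|---|
| 10 and 10 | 90.8% | 91.5% |
| 20 and 20 | 90.9% | 93.2% |
| 30 and 20 | 89.6% | 93.6% |

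Monte Carlo error is about 0.5 points on each figure (√(0.9 × 0.1 / 4,000)). Type I error was 4.6% to 5.7% with or without the covariates.

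**5. Chance imbalance.** For q = 0.5 the between-group difference in prevalence has SD √(2 × 0.25 / 126) = 6.3 points, so a 1.96-SD imbalance is 12.3 points. It moves the crude risk difference by 0.123 × 10 = 1.2 points when the risk gap is 10 points, and by 0.123 × 30 = 3.7 points when the gap is 30.

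**Limit of the check.** Steps 2 and 4 start from a model without age and community. The planned model has both, so the relevant R2 is what severity explains beyond them, which may be less.

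**The case against.** The strongest reply is that the plan is sound as written. It adjusts for the minimisation factors and the other intervention, reports crude and adjusted results, keeps type I error nominal and reaches its power. Some richer model nearly always exists. The gain rests on an R2 that the article does not supply. A severity-adjusted sensitivity analysis may also sit in a full analysis plan that is not shown. Most of this stands, and it limits the point to a recommendation. It does not remove it: the covariate list is closed, the measurements exist, and the cost is small.

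A reader might infer four stronger things that the document does not support.

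- **That the estimates are biased or the trial underpowered.** Randomisation keeps the planned analysis valid, and step 1 reproduces the stated power.
- **That chance imbalance leaves an unaccounted error.** The unadjusted interval already allows for it. The 1.2 to 3.7 points in step 5 compare with a half-width of 11.8.
- **That the number of affected ears is on record.** Entry requires CSOM in one ear or more, and each discharging ear is washed in the wash groups, so laterality was probably noted. No section names it as a variable.
- **That bilateral disease must raise child-level failure.** With 60% failure per ear (assumed), failure with two affected ears is 1 − [0.4² + ρ × 0.24]: 84% at ρ = 0, 67% at ρ = 0.7, but 60% at ρ = 1, the same as one ear. The illustration also gives the initially unaffected ear no risk, although the endpoint counts any discharge. Laterality is plausibly prognostic, not necessarily so.

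Two costs raised against the change are real: extra terms can stop log- and identity-link binomial models converging, and complete-case analysis (Missing data) would drop children who lack a baseline covariate. Both can be handled.

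**Conclusion.** The point holds as a modest loss of precision in an otherwise valid primary analysis. The adjusted model leaves out baseline perforation size, discharge amount and category of CSOM. If these are prognostic, the plan forgoes about 0.5 to 5 points of power and a reduction in half-width from 11.8 to between 11.7 and 10.6 points, for R2 of 0.02 to 0.20.

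This assumes 70% v 50% failure and 126 evaluable children per group. It also assumes that severity predicts failure beyond age and community, for which the article gives a qualitative hint and no figure. If severity is weakly prognostic, or largely tracks age and community, the gain is near the lower end or below it.

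**What to change.** Before outcomes are compared by arm, and before the oral comparison is unblinded, extend the closed list under Primary clinical outcomes along these lines:

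> The adjusted model will include age group, community, the other intervention, baseline perforation size and baseline amount of discharge (or category of CSOM), and unilateral or bilateral disease if recorded at the baseline ear examination. The adjusted risk difference and relative risk will be obtained by standardisation from a logistic model. Children with a missing baseline covariate will be kept by means of a missing category.

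State how a child-level severity value is formed when both ears are affected, for example from the worse ear. The crude estimates can stay as planned.

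The cost is a few more parameters, a different estimator for the adjusted result, slightly more programming, and the missing-covariate rule. No new data are needed. Doing it now matters because adding severity after an imbalance has been seen would look data-driven. If the sponsor prefers to keep the present adjusted model, the same model as a pre-specified sensitivity analysis is the minimum.
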